### Ethical considerations

Before participating, each patient receives and signs an informed consent form, which describes the details of the intervention and assessments. Participants are informed that they may cease participation at any time without consequences. In addition, participants are offered standard psychotherapy at our outpatient clinic if needed. The Ethics committee of The German Association of Psychology (DGPS, WR 052010_1) approved this trial.

## Discussion

### General

Despite the demonstrated efficacy of cognitive behavioral interventions for the treatment of CLBP [4], research on the efficacy of EXP is lacking [16]. To our knowledge, this is the first study to implement EXP in an outpatient setting in Germany. Furthermore, it is the first randomized clinical trial to evaluate EXP compared to cognitive behavioral treatment as usual for chronic pain. This comparison allows us to investigate whether fear-avoidant back pain patients benefit more from a treatment that addresses their specific pain-related fears than from a general psychological pain management program.

EXP is a relatively new approach for treating CLBP. During the process of developing and testing new interventions, it is important to investigate feasibility, cost-effectiveness and the underlying mechanism of treatment change. A recent review called for additional RCTs investigating approaches to CLBP [15], and with one exception [54], existing published RCTs have not investigated mechanisms of change [17]. To understand the process of change during EXP, the current RCT adds weekly measures of potential key mediators, such as self-efficacy, pain coping and pain beliefs. A novel feature of the current study is the inclusion of a short form of exposure therapy (10 sessions) in addition to a long version comprising 15 sessions. The analysis of the dose–response relationship in exposure treatment is crucial to determining an effective and economical treatment length. Finally, as EXP represents a completely new approach in the German health care system, information about cost-effectiveness is very important. In general, information on the economic aspects of CLBP treatments is lacking [5,22]. Accordingly, we integrated cost-effectiveness analysis with an adapted version of the TIC-P [51].

### Potential strengths of the study protocol

Participants will be recruited over a period of two years, which allows the inclusion of a larger sample (108 participants) relative to a prior RCT (N = 59) [12].

Before administering the intervention, the therapists participated in two workshops taught by [name] and [name], the developers of *in vivo* exposure for CLBP. This training ensures that therapists have basic knowledge and competence in implementing the treatment. Weekly supervision is provided, and therapeutic difficulties are discussed as a team. In addition, our research team is in regular contact with the groups in Maastricht and Leuven. Regular meetings allow discussion of specific difficulties with treatment implementation. It has been observed that the quality of treatment is frequently neglected in studies evaluating therapeutic interventions [4,16]. Accordingly, to improve the quality of the treatment protocol, adherence will be assessed through video-recordings of sessions and will be controlled in analyses. The Method of Assessing Treatment Delivery (MATD) proposed by Leeuw and colleagues [30] will be used to assess treatment fidelity.

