### Intervention

We translated and adapted the protocol of [name] and [name] [7] for implementing EXP in a German outpatient setting. The intervention is delivered by two PhD students who are clinical psychologists and who received two different sessions of training from [name] and [name]. In addition, each session is supervised afterwards by experienced psychologists. The control condition is a cognitive behavioral treatment for pain patients containing basic elements for the management of chronic pain that are standard in our outpatient clinic. The treatment includes graded activity, relaxation (progressive muscle relaxation) and cognitive interventions such as cognitive restructuring (Table 1). Both interventions are offered in a structured, individual setting with weekly appointments of 50 minutes.

**Table 1 T1:** Overview treatment sessions

**Session**	**EXP_long**	**EXP_short**	**CBT_P**
1	Anamnesis	Anamnesis	Anamnesis
2	Psycho-educational part I	Psycho-educational part I	Psycho-educational part I
3	Psycho-educational part II:	Psycho-educational part II:	Goal setting
	Fear-avoidance model	Fear-avoidance model	
4	Fear hierarchy	Fear hierarchy	Behavior analysis
5	Exposure 1	Exposure 1	Graded Activity I
6	Exposure 2	Exposure 2	Graded Activity II
7	Exposure 3	Exposure 3	Health Behavior
8	Exposure 4	Exposure 4	Progressive Relaxation I
9	Exposure 5	Exposure 5	Progressive Relaxation II
10	Exposure 6	Completion	*Cognitive Intervention I:* Attention Shifting
11	Exposure 7		*Cognitive Intervention II:* Identification of automatic thoughts and core beliefs about pain
12	Exposure 8		*Cognitive Intervention III:* Restructuring of dysfunctional thoughts and beliefs
13	Exposure 9		Individual Session I
14	Exposure 10		Individual Session II
15	Completion		Completion

CBT-P, Cognitive behavioral treatment for chronic pain problems*;* EXP*,* Exposure treatment.

Treatment sessions are video-recorded and a random selection of videos is evaluated for treatment fidelity. Two blinded raters independently assess protocol adherence, treatment contamination and whether the treatments can be differentiated from each other using the method of assessing treatment delivery in clinical trials (MATD) [30]. In advance, treatment elements of both treatments were identified and listed in a randomized order for the ratings.

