### Data collection

Data are collected at baseline (T0), after 10 sessions (T1, completion of EXP short), upon completion of the intervention (T2), and six months following completion of treatment (T3). Thus, participants in the short version of EXP complete only three assessments. Questionnaires are completed at home via the internet. This procedure reduces missing data and helps to keep study therapists blind to outcome data. Supplemental evaluations are carried out weekly, including process variables. If patients do not have internet access the assessment are provided on a computer in our outpatient clinic. Video recordings are carried out during each session to gather objective data for later analysis of treatment fidelity.

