### Data analysis

The latest version of The Statistical Package for Social Science (IBM SPSS Statistics) version 19is used for data analyses. Intention-to-treat analyses (ITT) used to account for deviations from random allocation and missing data. A repeated measures design will be used with primary and secondary measures as dependent variables, group as the between-subjects factor, and time of measurement as the within-subjects factor.

Possible confounding variables (for example, duration of complaints) will be considered and included as covariates according to the results of correlation analyses. Effect sizes (Cohen´s d) will be calculated to determine the magnitude of the mean differences between groups on the outcome variables. According to Cohen´s guidelines, an effect size of .2 indicates a small effect, .5 a medium effect and .8 a large effect [52]. We consider a 30% reduction on the NRS to indicate clinically important change on the core outcome measure of pain intensity [53]. The economic evaluation consisted of a cost-utility analysis and a cost-effectiveness analysis. For both analyses, the incremental cost-effectiveness ratio (ICER) was calculated as (C1-C0)/(E1-E0) where C is the cost and E is the effect and the experimental and comparator conditions are indexed with the 1, 0 subscripts.

The incremental cost-utility ratio will focus on the net costs per quality adjusted life years (QALY) gained. The cost-effectiveness ratio focuses on the net costs per reliable and clinically improved case of disability/pain. Probit analysis will be used for dose–response effects. This approach based on probability theory and includes determining the observed rates and resulting probability of a response for a particular treatment.

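### The promise to control for adherence names no analysis, and the covariate rule is not limited to baseline variables, so the EXP v CBT-P contrast may be adjusted for a post-randomisation variable

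*Protocol article*

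**What the plan says.** Five statements in the protocol article bear on this.

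- **Use of adherence** (Potential strengths of the study protocol): "adherence will be assessed through video-recordings of sessions and will be controlled in analyses". No outcome, model or analysis set is named, and there is no restriction to secondary or exploratory use.
- **Source of the ratings** (Intervention; Data collection): "Treatment sessions are video-recorded and a random selection of videos is evaluated for treatment fidelity", while "Video recordings are carried out during each session to gather objective data for later analysis of treatment fidelity". So every session is recorded, but only some recordings are rated. "Two blinded raters independently assess protocol adherence, treatment contamination and whether the treatments can be differentiated from each other".
- **Main model** (Data analysis): repeated measures with "group as the between-subjects factor, and time of measurement as the within-subjects factor". Adherence is not listed.
- **Covariate rule** (Data analysis): "Possible confounding variables (for example, duration of complaints) will be considered and included as covariates according to the results of correlation analyses". The example is a baseline characteristic, but the rule does not say that only baseline variables qualify.
- **Analysis principle** (Data analysis; Sample size calculation): "Intention-to-treat analyses (ITT) used to account for deviations from random allocation and missing data". The sample size section adds that dropouts stay in.

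**The concern.** Research question 1 asks whether exposure works better than CBT-P, and randomisation with an ITT analysis answers it. Adherence is scored from what happens in treatment sessions, so it comes after randomisation, and it describes delivery of the treatment that was assigned. It may also reflect the patient. Under EXP - unique features, exposure goes ahead only if the patient has understood the rationale and is willing. Under Additional variables, therapists record when they think the assigned approach does not fully suit the patient.

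If such a variable enters the model as a covariate, the group term compares arms at equal adherence. That is not the effect of assignment. It can show a difference where there is none, or hide part of a real one. The covariate rule offers no protection. If its correlation analyses are correlations with outcome, adherence would qualify just when it is associated with outcome, which is one of the two conditions for a shift.

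A second, conditional issue is coverage. A patient with no rated video has no score, and a complete-case adjusted model would leave that patient out.

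**Working it through.** The plan gives no figure to reproduce, so all inputs marked as assumed are illustrations.

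**1. Is adjustment open under the text?** The strengths section promises control for adherence and names no analysis. The Data analysis section neither lists adherence nor excludes it, and its covariate rule has no baseline restriction. Adjusting the EXP v CBT-P contrast for adherence is therefore permitted, though not stated outright.

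**2. Size of the shift.** In a linear model with a common slope,

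adjusted contrast − unadjusted contrast = −(arm gap in mean adherence, SD) × (within-arm slope of outcome on adherence).

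In SD units the slope is the within-arm correlation r. Assume that adherence has no effect on outcome, that it correlates −0.4 with an unmeasured severity factor, and that this factor correlates 0.5 with outcome. Then r = −0.4 × 0.5 = −0.20. With no true treatment difference:

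| Arm gap in adherence (assumed) | False shift, absolute value |
|---|---|
| 0 | 0 |
| 0.5 SD | 0.20 × 0.5 = 0.10 SD |
| 1.0 SD | 0.20 × 1.0 = 0.20 SD |

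The sign depends on which arm has the higher adherence. For scale, the Data analysis section calls d = .2 a small effect.

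**3. Effect on the test, 36 v 36 and no true difference.** The standard error of the adjusted contrast is √[(1 − r²) / (18 × (1 − R²))]. Here 18 = 36 × 36 / 72, and R² = 18 × gap² / (18 × gap² + 72) is the share of the group indicator explained by adherence.

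- Gap 0.5: R² = 4.5/76.5 = 0.059; SE = √(0.96/16.94) = 0.238; shift/SE = 0.42; two-sided 5% rejection rate about 7%.
- Gap 1.0: R² = 18/90 = 0.20; SE = √(0.96/14.4) = 0.258; shift/SE = 0.775; rejection rate about 12%.

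With both exposure arms pooled (72 v 36), the same inputs give about 8% and 15%. At the far end of the range tried (r = 0.4, gap 1.0 SD, 36 v 36), the shift is 0.40 SD and the rejection rate about 38%.

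**4. Coverage.** If all sessions take place there are 36 × 15 + 36 × 10 + 36 × 15 = 1440 videos. The share rated is not given. Suppose videos are drawn at random without regard to patient, each with probability q. The chance that a patient has no rated video is then (1 − q)^sessions.

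| q (assumed) | No rating, 15 sessions | No rating, 10 sessions | Expected unrated of 108 |
|---|---|---|---|
| 5% | 0.463 | 0.599 | 72 × 0.463 + 36 × 0.599 ≈ 55 |
| 10% | 0.206 | 0.349 | 72 × 0.206 + 36 × 0.349 ≈ 27 |
| 20% | 0.035 | 0.107 | 72 × 0.035 + 36 × 0.107 ≈ 6 |

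Under this scheme the 10-session arm would lose more patients than the 15-session arms. Patients who stop early have fewer videos and are more likely to be unrated, yet the ITT set is meant to keep them. If videos were sampled within each patient, treated patients would not be lost in this way.

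**The case against.** The strongest defence is that the text does not say the primary comparison will be adjusted. The clause sits in a Discussion paragraph about training, supervision and treatment quality. The Data analysis section, which specifies the model, does not mention adherence. Fidelity is listed under Additional variables, and the recordings are said to serve an analysis of fidelity. On that reading, controlled could mean checked, or could refer to a supplementary analysis. Part of this stands: adjustment of the primary model is an inference. But the sentence already covers checking when it says adherence will be assessed. Controlling it in analyses, as a separate step, most naturally means statistical adjustment. If checking was meant, the wording still needs correcting.

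A reader might infer four stronger points, which the documents do not support:

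- *The plan contradicts its ITT commitment.* It would do so only if an adherence-adjusted result replaced the ITT result. An adjusted analysis reported beside it would not, and the text does not say which is intended.
- *Adherence must differ by arm because each arm is rated on its own elements.* The Intervention section says that elements of both treatments were listed in randomised order for blinded raters. No arm difference is documented, and without one there is no shift.
- *Adherence is known to depend on prognosis.* The sections cited above make this plausible; they do not establish it.
- *An adjusted analysis necessarily loses patients.* The selection is of videos, not patients, and the sampling unit, scoring and handling of missing scores are not given. An article may leave those to the full protocol.

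It is also fair to say that the shift at the lower end, 0.10 SD, is less than half the unadjusted standard error of a 36 v 36 difference (√(2/36) = 0.236 SD).

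**Conclusion.** The point holds as a fault in a stated rule. The article promises to control for a post-randomisation variable, names no analysis, and has a covariate rule that would let the variable into the effectiveness model. If adherence differs between arms and is related to prognosis, the adjusted EXP v CBT-P contrast does not estimate the effect of assignment. Under the assumed correlation of 0.2 and gap of 0.5 to 1.0 SD, the false shift is 0.10 to 0.20 SD, which is half to all of what the article calls a small effect. It is zero if there is no gap. Loss of patients without a score is possible and depends on the sampling scheme. The article does not state that the primary model is adjusted, so that should not be reported as fact. The text should be changed before analysis.

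**What to change.** Replace the clause about controlling adherence with a statement that the ITT effectiveness comparisons are not adjusted for adherence. In the Data analysis section, limit covariates to variables measured at baseline. Report adherence, contamination and differentiation descriptively by arm. If an analysis using adherence is wanted, label it supplementary and non-randomised, and state its estimand, how videos are sampled, and how patients without a rated video are handled.

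This costs wording only, with no change to sample size, data collection or fidelity rating. The Trial status section reports 71 participants randomised by May 2013 and data expected in 2014, so the change could be made before analysis.

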### Potential limitations of the study protocol

The treatment in the present study is designed for patients with CLBP with sufficient levels of fear and avoidance (TSK ≥35, Phoda-profile), and thus it is unclear whether results are likely to generalize beyond this specific pain population. Nevertheless, we attempted to keep the eligibility criteria very liberal (that is, no exclusion for comorbidities or medication use, moderate level of TSK) to offer broad access to the intervention. Secondly, the present study relies largely on self-report measures.

## Conclusions

It is important to determine whether a specialized treatment is needed for fear-avoidant back pain patients, a high-risk group characterized by substantial impairment, or whether standard CBT programs are adequate? This RCT provides an opportunity to address this question by investigating whether *in vivo* exposure is more effective than psychological treatment as usual for the treatment of CLBP. Furthermore, the results of this study will be used to establish the feasibility and cost-effectiveness of *in vivo* exposure in an outpatient psychological setting.

### Trial status

Recruitment of patients started on August 2011 and will proceed until the end of 2013. Data on the effect, process and economic evaluation are expected to be available in 2014. A total of 71 participants had been enrolled and randomized for this trial by May 2013 (Figure 1).

**Figure 1 F1:**
[figure not shown]
Flow of participants (07/06/2013).

## Abbreviations

CBT-P: Cognitive behavioral treatment for chronic pain; CEQ: Credibility and expectancy questionnaire; CLBP: Chronic low back pain; EQ-5D: EuroQol questionnaire; EXP: Exposure; FESS: Pain self efficacy questionnaire; HADS: Hospital anxiety and depression scale; ICER: Incremental cost-effectiveness ratio; IMMPACT: Initiative on methods measurements, and pain assessment in clinical trials; IPAQ: International physical activity questionnaire; ITT: Intention-to-treat analyses; MATD: Method of assessing treatment delivery in clinical trials; NRS: Numeric rating scale; PASOL: Pain solutions questionnaire; PASS: Pain anxiety symptom scale; PCS: Pre-stratified by degree of pain catastrophizing; PDI: Pain disability index; PHODA: Photo series of daily activities; PIPS: Psychological inflexibility in pain scale; PVAQ: Pain vigilance and attention questionnaire; QALY: Quality adjusted life years; QBPDS: Quebec back pain disability scale; RCT: Randomized controlled trial; SPSS: Statistical program for social science; TIC-P: The trimbos/iMTA questionnaire for costs associated with psychiatric illness; TSK: Tampa scale of kinesiophobia
